### Study design

A community-based quasi-experimental study design was chosen to assess differences in key variables between the intervention and control arms. We chose a quasi-experimental design for several reasons. We lacked information about clear randomization unit given the characteristics of individuals or clusters (woredas), and it was likely that many woredas in Oromia region are not homogenous towards our outcomes of interest. Another reason was due to resource constraints, as we did not have a sufficient number of woredas in our study to conduct a pure randomized trial design. The study included two waves of data collection from a panel of recruited pregnant women at Phase 1. We attempt to leverage Phase 1 findings to inform the development of study tools and identify factors affecting implementation to provide insights into the improvement our intervention at Phase 2. This study is registered at ClinicalTrial.gov (NCT05907720).

In Phase 1, we conducted the baseline survey with 470 pregnant women enrolled in intervention and control arms in January 2024. After the baseline survey, we implemented a set of HCD prototype solutions in the intervention arm only, keeping the usual standard of care intact in the control arm. After the 4-month period of HCD solution implementation, we conducted the midline survey among the same women in the panel from both the intervention and control arms. In the midline survey, we interviewed 453 pregnant women, with 17 pregnant women lost to follow-up. The midline assessment also included in-depth interviews with purposively selected pregnant women from the panel and health workers who engaged in implementation.

In Phase 2, we will conduct a post-only study with a new sample of vulnerable pregnant women who will be recruited after the implementation of refined HCD solutions. Since the focus is on enhancing implementation feasibility, scalability, and health system ownership of Phase 1 solutions, which have already shown significant improvements in institutional delivery, we believe a post-only assessment is sufficient to observe consistent effectiveness. 

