We will compare outcomes between the intervention and control arms at end-line, and the end-line findings will also be compared with the baseline to identify whether refined solutions bring greater impact than our initial solutions did in Phase 1. Thus, our overall study design includes three waves of data points: baseline and midline assessments in Phase 1 and end-line assessment in Phase 2. The study design is further described in
Figure 2.

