### Recruitment

After obtaining a list of all interested women from health extension workers and health development armies, data collectors visit the women in person to screen their pregnancy status and vulnerability level to assess their eligibility. With the woman’s verbal consent, the data collector administers the pregnancy screening tool to identify her pregnancy status. Only women at 5+ months of pregnancy and aged 15–49 are considered eligible. If eligible, she is screened for her vulnerability level, assessed through the vulnerability screening tool. Those considered to be moderately to highly vulnerable are eligible and entered into the sampling frame. Women who score at least 9 out of the maximum 20 vulnerability screening questions will be identified as a study participant. All responses to the screening questions will be entered into the data collectors’ mobile phone application that automatically determines pregnant women’s eligibility during the visit. 

All eligible women are entered into our sampling frame. After listing eligible pregnant women, we aim to recruit approximately three women per enumeration area to achieve our target sample size. If an enumeration area has five or fewer eligible women, they are all contacted for recruitment. If there are more pregnant women than the minimum required number of pregnant women, we randomly select the required number. If a woman is not interested or available for participation, we contact the next randomly selected woman for recruitment. Recruitment continues until our sample size is reached, expanding to other enumeration areas if necessary. Recruitment in Phase 1 was completed in this way, and Phase 2 recruitment will follow this procedure.

For the qualitative assessment, recently delivered women who receive our intervention and health workers in the intervention sites are purposively recruited. Purposive selection of the sample allows us to understand the experiences of engaging in our implementation process among diverse individuals. For women, the selection criteria include: 1) residing in Siraro and Shalla woredas, 2) being exposed to the HCD solutions during their last pregnancy, and 3) having delivered after receiving the solutions. To further obtain diverse and in-depth experiences among our sample, we prioritize recruiting women who are in earlier gestational ages (5

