### Data collection and measurement

**
*Survey interview*.** All participants from Phases 1 and 2 undergo a one-on-one survey interview to assess sociodemographic information, psychological factors, social and structural factors, and maternal health service utilization. A structured interview is administered by a local data collector in the local language. The survey captures the self-reported place of the most recent childbirth along with uptake and frequency of ANC visits during the most recent pregnancy. Secondary outcomes include knowledge, attitudes, and perceptions about maternal health service utilization, social norms, gender norms, spousal dynamics, decision-making, and community and structural factors. Midline (post-intervention in Phase 1) and end-line (post-intervention in Phase 2) assessments additionally include questions measuring program exposure.

**
*Qualitative interview*.** Purposively selected women from the study participants (n=20) along with health workers (n=32) engaged in the program participate in an in-depth interview. Given the 4-month duration of program implementation among pregnant women in their 5
^th^ or higher months of pregnancy, interviews are administered to recently delivered women inquiring about their perceived effects of the intervention on the place of childbirth and ANC uptake during pregnancy. Additionally, the interview guides for women and health workers contain questions around key implementation research outcomes, including acceptability and feasibility, to identify any similarities and differences arising across different types of interview participants.

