Nevertheless, this study will use a multi-level modeling framework to assess the intervention effect based on a difference-in-difference analysis by computing differences between baseline and midline within each arm, and then test this difference between intervention and control arms. A fixed effects model will first be used to observe this effect of the intervention. Kebele and PHCU will then be included as random intercepts to account for clustering within these levels. The estimated variance for random effects will show the amount of variability in the outcome that is explained by the clusters (i.e., how much of institutional delivery uptake is attributed to a kebele). If the coefficient of the interaction term is significant with the significant model fit, we will observe significant program effects. The identical analyses will be conducted with 4+ANC visits as the outcome variable. Other covariates will be included by comparing goodness-of-fit statistics (e.g., AIC, BIC) to improve the model fit. Proper model specification and diagnostic tests will be conducted to enhance the robustness of the results. Phase 2 data analysis will focus on comparing service utilization between intervention and control arms. Since we expect that study effectiveness will be stronger in Phase 2 with the implementation of enhanced solutions, we will also compare the study outcomes with baseline at Phase 1.

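### End-line is compared with a baseline taken before any solution was delivered, so it cannot show whether the refined solutions beat the initial ones

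*Protocol article*

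**What the plan says.** The Study design section sets out three waves: baseline and midline in Phase 1, end-line in Phase 2.

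- **Timing of baseline.** "After the baseline survey, we implemented a set of HCD prototype solutions in the intervention arm only". Baseline therefore precedes every solution.
- **Midline.** The same panel was surveyed in both arms after four months of the initial solutions: "we interviewed 453 pregnant women, with 17 pregnant women lost to follow-up".
- **Phase 2.** "we will conduct a post-only study with a new sample of vulnerable pregnant women", recruited once the refined solutions are in place.
- **The comparison at issue.** Besides the arm comparison at end-line, "the end-line findings will also be compared with the baseline to identify whether refined solutions bring greater impact than our initial solutions did".

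The Data analysis plan makes the end-line arm comparison the focus of Phase 2. It then adds: "we will also compare the study outcomes with baseline at Phase 1". The reason it gives is an expectation: "we expect that study effectiveness will be stronger in Phase 2 with the implementation of enhanced solutions". Midline appears in that section only in the Phase 1 difference-in-difference.

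**The concern.** The plan states a question (do the refined solutions do better than the initial ones?) and a comparator (the Phase 1 baseline), and the two do not match. A gain over baseline shows that something changed since before any solution existed. It does not show that the second version did better than the first.

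Phase 2 aims to make the solutions cheaper, less intensive and easier for the health system to own. Refined solutions that scale better but work no better, or somewhat worse, are therefore a real possibility. End-line could still exceed baseline in that case and be reported as greater impact. According to the abstract, the findings go to the Ministry of Health to inform national implementation.

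**Working it through.** **1. What each contrast contains.** Let B, M and E be the institutional delivery rate at baseline, midline and end-line.

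- E − B is the refined solutions plus change over time, against no solution. M does not enter.
- Refined minus initial is (E − B) − (M − B) = E − M. The baseline cancels and the midline is required. Neither section names E versus M.

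**2. What the baseline outcome is.** "The survey captures the self-reported place of the most recent childbirth" (Data collection and measurement). "Only women at 5+ months of pregnancy" were eligible (Recruitment), and all were still pregnant at baseline. Read as worded, the baseline value concerns an earlier birth, and first-time mothers have none.

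**3. Inputs.**

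- From the protocol: 48% and a 9-point effect, alpha 0.05, ICC 0.009, 531 per arm in Phase 2 with 10% non-response, 470 women at baseline, 453 at midline, 80 enumeration areas per arm in Phase 1 and about 106 in Phase 2.
- Assumed: equal arms in Phase 1 (235 at baseline, 226.5 at midline), 106 areas per arm in Phase 2, independent samples, two-sided tests, and the size of any secular change, for which the documents give no figure.

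**4. The plan's own figure.** A two-sided test of 48% against 57% with 80% power and pooled variance under the null needs 483 per arm. With 10% non-response that is 483 × 1.1 ≈ 532, or 483 / 0.9 ≈ 537. The stated 531 is thus reproduced closely, with no design effect. It is sized for the end-line arm comparison and not for refined versus initial.

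**5. Design effects within enumeration areas.**

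- Phase 1: m = 470/160 = 2.94, so 1 + 1.94 × 0.009 = 1.017.
- Phase 2: m = 531/106 = 5.01, so 1 + 4.01 × 0.009 = 1.036.
- End-line responders: 0.9 × 531 ≈ 478 per arm.

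**6. Probability that E differs from B at p<0.05, intervention arm.** SE = sqrt(0.48 × 0.52/235 × 1.017 + p(1 − p)/478 × 1.036), where p is the end-line rate.

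| Scenario | p | Difference | SE | Probability |
|---|---|---|---|---|
| Refined = initial, no secular change | 57% | 9 | 4.01 | 61% |
| Refined = initial, +3 points secular | 60% | 12 | 4.00 | 85% |
| Refined = initial, +6 points secular | 63% | 15 | 3.98 | 96% |
| No Phase 2 effect, +6 points secular | 54% | 6 | 4.02 | 32% |

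The last row also describes refined solutions 3 points worse than the initial ones with no secular change. Refinement adds nothing in any row.

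**7. Subtracting the control arm.** SE = sqrt(2 × 0.48 × 0.52/235 × 1.017 + (0.57 × 0.43 + 0.48 × 0.52)/478 × 1.036) = 5.69 points. With a 9-point effect in both phases, the probability is 35%. A shared trend is removed, but the reference is still no solution.

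**8. The contrast that matches the question.** (Intervention − control at end-line) − (intervention − control at midline), which has expected value 0 when the two effects are equal. Rates are 57% and 48% in both waves.

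| Clustering | SE midline | SE end-line | SE contrast | 95% half-width |
|---|---|---|---|---|
| None | 4.67 | 3.22 | 5.67 | 11.1 |
| Enumeration areas | 4.71 | 3.27 | 5.74 | 11.2 |
| Ten clusters per arm (assumed; design effects 1.19 and 1.42) | 5.11 | 3.84 | 6.39 | 12.5 |

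If only 80% of the midline women had delivered, the unclustered half-width is 12.0. Ignoring clustering, the smallest extra gain detectable with 80% power is about 16 points, and power for an extra 9 points is about 35%.

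**The case against.** **A milder reading exists.** The Study design sentence refers to what the initial solutions achieved in Phase 1, and the Data analysis plan measures that as a baseline-to-midline change. Baseline could be meant as a common reference for two changes. That reading is coherent, but it reduces to end-line versus midline, which neither section names. It supports the correction.

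**The percentages test a rule the protocol does not state.** No significance test of end-line against baseline is specified, and 61% is simply the power to detect a real 9-point effect against no intervention. This is fair. The percentages show how easily the comparison could mislead and are not error rates of a planned test. The single-arm figures also ignore control data; with those data the figure is 35%. The 48% is a national average, applied here to a sample selected for vulnerability.

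**The question is peripheral.** It is not one of the three evaluation objectives, and the concurrent Phase 2 arm comparison is untouched. This limits the weight of the point but does not make the stated contrast right.

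**The replacement is imprecise and confounded as well.** This stands. The phases still differ in sample, calendar time, design and programme window (four months against six, probably minor given the fixed visit schedule and entry at five months or later). The new contrast can only be descriptive. Because the samples are new and not randomised, covariate adjustment is also needed.

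**The earlier-birth argument also touches the Phase 1 difference-in-difference and depends on questionnaire wording not shown.** Both are true. The main point does not need it.

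**Conclusion.** The concern holds. As written, the comparison cannot answer the question attached to it, because the reference wave precedes the initial solutions and carries nothing about them. This follows from the wording of the two sections and needs no numerical assumption.

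The size is illustrative. With equal true effects of 9 points from 48%, and any p<0.05 difference read as greater impact, the plan would credit refinement with a gain it did not produce 61% of the time with no secular change and 85% to 96% with assumed rises of 3 to 6 points. The figure is 35% if the control arm is subtracted. Some secular change is plausible, since the Introduction describes a 2020 to 2025 national plan that also aims to reduce home births, but its size is unknown.

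The point concerns a secondary claim. The end-line comparison of intervention with control is not affected.

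**What to change.** In the Study design section and the Data analysis plan, replace end-line versus baseline with a contrast of two between-arm differences: intervention minus control at midline, among Phase 1 women who have delivered, and intervention minus control at end-line in Phase 2. Report it for institutional delivery and for four or more ANC visits. Give a 95% confidence interval that allows for kebele and PHCU clustering, and adjust for the confounders that the plan already intends to control. Label the contrast descriptive, and state that a larger Phase 2 difference will not be attributed to refinement alone. A simpler alternative is to keep the baseline comparison as pure description and drop the claim about greater impact.

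The cost is rewording in two places and one extra estimate from data already collected or planned. The sponsor gives up a stronger-sounding claim for an imprecise one, with a half-width of about 11 points or more against a 9-point planning effect. The midline difference is not baseline-adjusted, so it will not equal the Phase 1 difference-in-difference estimate; the two should be shown side by side.

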**Figure 2. f2:**
[figure not shown]
Quasi-experimental evaluation study among vulnerable pregnant women.

### Sample

Our primary target participants are vulnerable pregnant women aged 15–49. For consent administration, we segmented adult pregnant women aged 19 and above, pregnant adolescent girls aged 15–18, and service providers. Service providers, such as midwives, health extension workers and health development armies who had engaged in the study were recruited for qualitative assessment at midline (Phase 1) and will be enrolled in end-line (Phase 2).
Table 1 below summarizes inclusion and exclusion criteria for each sample population.

**Table 1. T1:** Summary of inclusion and exclusion criteria of study sample.

Respondent type	Inclusion criteria	Exclusion criteria
Pregnant women	Women in their 5th or higher months of pregnancy; meet the high vulnerability criteria.	Pregnant women who are less than 5 months pregnant; meet the low vulnerability criteria.
Women who delivered recently (Midline and end-line only)	Recently delivered women included in the panel for baseline assessments during Phase 1; those who have received HCD solutions during Phase 2; meet the high vulnerability criteria.	Recently delivered women who were not included in the panel; did not have exposure to HCD solutions; meet the low vulnerability criteria.
Heath Extension Workers	Who work in health promotion and essential maternal health services in heath posts.	Who have worked in this position less than 6 months in the intervention arm.
Health Development Armies	Community volunteers who work on early screening and health promotion activities for pregnant women.	Who have worked in this position less than 6 months in the intervention arm.
Head of woreda health office	Head/Vice Head of the woreda Health Office who help facilitate implementation of the project	Who have worked in this position less than 6 months in the intervention arm.

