**Methods:**

The study has two distinct phases. In Phase 1, HCD solutions were developed through co-design workshops with vulnerable pregnant women and key stakeholders. Final solutions included home visit education, audio programs promoting couple discussion, and print materials, implemented in collaboration with community health workers and health officers. A community-based, quasi-experimental, mixed-method study design was used to assess differences between intervention and control arms. A panel sample was enrolled after screening for pregnancy and vulnerability level and surveyed at baseline and midline in Phase 1. Phase 2 adopts an identical design approach with a focus on refining Phase 1 solutions. Newly recruited pregnant women will receive refined solutions for six months, which will be evaluated using post-only end-line surveys and in-depth interviews.

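### Table 1's exposure clause for recently delivered women contradicts the planned Phase 2 comparison of intervention and control arms and should be confined to the qualitative interviews

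*Protocol article*

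**What the plan says.** Table 1 (Methods, Sample) has a row headed "Women who delivered recently (Midline and end-line only". For Phase 1 it admits women from the baseline panel. For Phase 2 it admits "those who have received HCD solutions during Phase 2". Its exclusion cell reads "Recently delivered women who were not included in the panel; did not have exposure to HCD solutions; meet the low vulnerability criteria". Neither cell names an arm or a type of interview.

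Other sections describe a two-arm Phase 2:
- Study design: "We will compare outcomes between the intervention and control arms at end-line".
- Sample size calculation: 531 women per arm at a 1:1 ratio, for a 9-point difference with 80% power.
- Data analysis plan: the Phase 2 analysis centres on service use in intervention versus control.
- Recruitment: survey women qualify on age, gestation and vulnerability score. Exposure is required only of women chosen for the qualitative interviews.
- Data collection and measurement: the midline and end-line surveys measure programme exposure as a variable.

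On timing, the Abstract says "Newly recruited pregnant women will receive refined solutions for six months". Study design speaks of "a new sample of vulnerable pregnant women who will be recruited after the implementation of refined HCD solutions". Recruitment, which screens for pregnancy of five months or more, adds "Recruitment in Phase 1 was completed in this way, and Phase 2 recruitment will follow this procedure".

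**The concern.** Eligibility criteria decide who enters the comparison. A rule that requires receipt of the intervention cannot be met by women in control woredas, so field staff who followed Table 1 to the letter would have no one to enrol there.

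The likely workaround is to apply the rule in the intervention woredas only. That sets women who were reached by the programme against all eligible women in the control woredas. Receipt happens after the intervention starts and may depend on things that also affect place of birth. The article says that women late in pregnancy may not be fully exposed and that home visits called for the husband to be present. Its Introduction lists family support and decision-making power among the factors that shape service use.

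The end-line contrast is the only concurrent comparison in Phase 2. The other planned comparison, with the Phase 1 baseline, is historical and cannot replace it.

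**Working it through.** **1. Does the sample size need a full control arm?** Inputs from Sample size calculation: 48% institutional delivery, a 9-point effect (so 57%), significance level 0.05, power 80%, 10% non-response. Two assumptions are added: the test is two-sided, and the 48%, which is stated for Phase 1, carries over to Phase 2.

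n per arm = [1.960 × √(2 × 0.525 × 0.475) + 0.842 × √(0.48 × 0.52 + 0.57 × 0.43)]² / 0.09²

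= [1.960 × 0.7062 + 0.842 × 0.7034]² / 0.0081 ≈ 482.1, rounded up to 483.

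483 × 1.1 = 531.3, against the stated 531. (Dividing by 0.9 gives 537.) The stated figure is therefore a two-arm calculation, and 2 × 531 = 1062 matches the total given. The plan needs 531 controls.

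**2. How many of them does Table 1 admit?**
- The Phase 1 control condition is explicit: "we implemented a set of HCD prototype solutions in the intervention arm only, keeping the usual standard of care intact in the control arm".
- The Abstract calls the Phase 2 design approach identical, so Phase 2 controls are taken to receive no solutions either. This is an inference, but a comparison with a control arm needs it.
- The Phase 2 inclusion route requires receipt, and the exclusion removes the unexposed. Eligible controls on a literal reading: 0 of 531.

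**3. Can another row supply the controls?** The row for pregnant women has no exposure clause. However, the outcome is the self-reported place of the most recent birth. With a single post-only survey, a woman who is still pregnant has no index delivery to report. End-line women who can supply the outcome therefore fall under the recently-delivered row.

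**4. Is the row qualitative only?** It does not say so. Its Phase 1 inclusion cell covers the whole baseline panel, which includes controls, whereas the qualitative sample comes from the intervention sites alone. If the row were qualitative only, Table 1 would hold no rule for end-line survey women who have delivered.

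**5. What if the clause is applied in the intervention arm only?** Let r be the share of eligible women reached, and g the difference in institutional delivery between reached and unreached women that would exist without the programme. Restricting the arm to reached women raises its untreated rate by (1 − r) × g. The documents give neither r nor g. The direction is upward if g is positive, which the reasons given under the concern make likely. No size can be put on it.

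**6. Timing.** If women are enrolled in pregnancy and then receive solutions for six months, they can report an index delivery at end-line. If they are first screened as pregnant after implementation and surveyed once, they cannot. The three timing statements do not settle which applies.

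**The case against.** The strongest reply is that nobody will run Phase 2 without controls. Study design, Sample size calculation and Data analysis plan all describe a control arm. The survey recruitment text has no exposure condition, and a survey that measures exposure has little reason to require it for entry. Phase 1 points the same way: the same row covers midline, yet midline interviewed 453 of the 470 panel women, from both arms. The wording closely resembles the qualitative criteria and has probably strayed from them. Table 1 is also only a summary.

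Most of this stands, and it limits what can be claimed. Four stronger readings are tempting, and the documents do not support them:
- **That Phase 2 has no control arm.** The zero in step 2 is what one table row yields when read alone. It does not forecast the trial.
- **That the panel clause bars every Phase 2 woman.** The inclusion cell separates the phases, with the panel for Phase 1 and receipt for Phase 2. The exclusion is naturally read the same way, so it needs a label and no more.
- **That the bias has a known size against the 9-point target.** Any figure would rest on invented values of r and g, and no analysis section describes an exposed-only analysis.
- **That the Abstract and Study design cannot both be right on timing.** Recruitment after implementation may mean after roll-out begins. The ambiguity is real but separate from the exposure clause.

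The reply does not remove the contradiction. The row is unlabelled, covers end-line, and is the row under which delivered survey women fall.

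**Conclusion.** The point holds as a contradiction in eligibility wording. Table 1 makes receipt of the solutions the only Phase 2 route in for recently delivered women, while the rest of the article plans a 1:1 end-line comparison at 531 per arm with no exposure condition for survey women.

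Followed literally, the row leaves no eligible controls. Followed in the intervention arm only, it selects that arm on a post-intervention event and probably tilts the result in its favour, by an amount that cannot be estimated. Followed in neither arm, as Phase 1 practice suggests, the comparison is unharmed and only the table is wrong.

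The conclusion assumes that Phase 2 controls receive no solutions and that outcome data come from women who have delivered. Phase 2 is still being prepared according to Study status, so the text can be put right before recruitment.

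**What to change.** 1. In Table 1, remove the exposure clauses from the survey criteria for recently delivered women. Keep them in a separate row labelled for the qualitative interviews.
2. Limit the panel clause to Phase 1.
3. State one eligibility rule for the Phase 2 survey and apply it identically in both arms.
4. State that Phase 2 survey women are analysed by arm, defined by woreda of residence, whatever their exposure. Report measured exposure descriptively.
5. Reconcile the Abstract, Study design and Recruitment on whether Phase 2 women are recruited before or after implementation, so that every woman surveyed has an index delivery to report.

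Items 1 to 4 need an amendment to one table row and a few sentences, and leave the 531 per arm unchanged. The price is that the estimate includes women the programme did not reach and may be smaller than an exposed-only estimate. Item 5 needs a clear statement of order. A design that enrols in pregnancy and follows to delivery is one way to meet it, but that would add tracing and attrition to a phase described as post-only, and removing the Table 1 contradiction does not require it.
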